### Blinding

As blinding of physicians and participants to allocation of treatment groups is impossible in the current design due to dissimilarity of interventions, only outcome assessors, statistician and data analysts will be blinded. The outcome assessors will not participate in treatment and a research nurse or KMD blinded to allocation will conduct outcome assessment in a separate room after treatment and will not attempt to become knowledgeable of allocation. The patient will also be cautioned against informing the outcome assessor of treatment allocation prior to each assessment. The electronic data transferred to statistician and data analysts will not contain information on treatment allocation.

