## Methods/design

The protocol of this pCRN study is presented in accordance with the 2013 SPIRIT (Standard Protocol Items: Recommendations for Interventional Trials) Statement (see Additional file 1 for the populated SPIRIT Checklist and Table 1 for the trial schedule of enrollment, interventions, and assessments in accordance with recommended SPIRIT figure).

**Table 1 Tab1:** Time points of each assessment index

	Study period										
Time point	Enrollment	Allocation	Active treatment post allocation						Follow-up		
	Week −1	Week 0 (Baseline)	Week 1	Week 2	Week 3	Week 4	Week 5	Week 6	Week 7	Week 10	Week 14
Enrollment											
Eligibility screening	○										
Written informed consent	○										
Vital signs	○								○	○	○
Sociodemographic characteristics, medical history (e.g., LBP, medication history)	○										
Physical examination	○										
Randomized allocation		○									
Interventions											
Treatment in CMT group			←2–3 times/week →				←1–3 times/week →				
Treatment in UC^a^ group (times/week)			←2–3 times/week →				←1–3 times/week →				
Treatment in CMT + UC^a^ group (times/week)			←2–3 times/week →				←1–3 times/week →				
Assessments											
Symptoms and change in medicine		○		○	○	○	○	○	○	○	
NRS of LBP and leg pain	○	○		○	○	○	○	○	○	○	○
ODI		○					○		○	○	
PGIC							○		○	○	
ROM		○					○		○	○	
EQ-5D		○					○		○	○	○
HUI-III		○					○		○	○	○
Economic evaluation		○					○		○	○	○
Adverse events		○	← every visit →						○	○	○

*CMT Chuna* manual therapy, *UC* usual care, *NRS* Numeric Rating Scale, *LBP* low back pain, *ODI* Oswestry Disability Index, *PGIC* Patient Global Impression of Change, *ROM* range of movement, *EQ-5D* EuroQol-5 dimensions, *HUI-III* Health Utility Index III

^a^UC: medication will be administered daily and physical therapy will be applied 2–3 times/week

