### Trial design and study setting

This pCRN study employs a multicenter, randomized, three-armed, parallel-group design. Participants will be randomly allocated to the *Chuna* manual therapy group, a usual care group, or a combined treatment group of *Chuna* manual therapy with usual care at a ratio of 1:1:1. Participants will be recruited at four major Korean medicine hospitals in Korea (Pusan National University Korean Medicine Hospital, Kyung Hee University Korean Medicine Hospital at Gangdong, Jaseng Hospital of Korean Medicine, and Mokhuri Neck and Back Hospital) and recruitment period is anticipated to be from February to August 2016. Participants will be recruited through each hospital website and online and offline advertisements. These study sites possess the facilities, personnel, and patient recognition required for LBP patient recruitment, and further information on the study sites is available at Clinical Research Information Service (CRIS registration number: KCT0001850). Participants will receive a total 6 weeks of outpatient treatment for LBP starting from visit 2 through random allocation if deemed eligible in screening at visit 1. General management and treatment processes will adhere to predetermined clinical trial procedures.

The entire research process, design, and setting were prepared through six or more meetings of 22 pCRN members including rehabilitation experts (*n* = 14), clinical research coordinators (*n* = 4), clinical research methodologists (*n* = 2), and economic evaluation experts (*n* = 2) currently employed at six university hospitals, two spine-specialty Korean medicine hospitals, and the Korea Institute of Oriental Medicine (see Additional file 2 for trial committee organization and contributions and role).

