### Randomization and allocation concealment

A statistician blinded to the objectives and exact design of this study will use SAS 9.3 to generate the allocation sequence using block randomization (block size = 6). Researchers will take care so that block sizes do not become known to the researchers who conduct participant recruitment or intervention allocation.

The researcher conducting participant recruitment at each site (Korean medicine doctor (KMD)) will contact the main trial site for central randomization by phone for random allocation to the three groups at a ratio of 1:1:1 of participants who have voluntarily agreed to participate in the trial, given written informed consent, and been screened and found eligible for trial participation in accordance with inclusion and exclusion criteria. Central randomization by phone will be performed through contact upon participant enrollment by the researcher conducting participant recruitment at each site to a designated independent researcher at the main trial site who will consecutively assign the randomized number and allocation group of each participant by verifying the sequence in the order of phone contact. All allocation numbers will be concealed through blinding of randomized number generation and central phone randomization.

The four sites will receive random allocation competitively on participant enrollment without stratification by site, and each site will respectively stop recruitment when the equal allocated number of 15 participants has been recruited.

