#### Secondary outcome measures

Secondary outcome measures include leg pain level for the past week as assessed using the NRS. Functional status will be evaluated using the Oswestry Disability Index (ODI) questionnaire. The ODI is a 10-item questionnaire developed for the purpose of LBP-related disability assessment [20]. Each item has a six-level answer choice, and each level correlates with a score of 0–5. Higher scores reflect greater disability. The accredited Korean version of the ODI [21] will be used. The Patient Global Impression of Change (PGIC) will be assessed for comprehensive and global assessment of change in LBP and movement limitation due to pain [18, 22]. The PGIC discerns subjective impression of change in seven levels ranging from 1 = very much improved; 2 = much improved; 3 = minimally improved; 4 = no change; 5 = minimally worse; 6 = much worse; to 7 = very much worse. While the PGIC was initially developed for psychological use, it is currently applied in pain evaluation of various medical fields. The EuroQol-5 dimensions (EQ-5D) health survey is a measurement tool for health-related quality of life and widely used across the health care sector. The range of scores is from −1, indicating health considered worse than death to 1, meaning perfect health [23]. The EQ-5D comprises five dimensions or items assessing current health state, which are mobility, self-care, usual activities, pain/discomfort, and anxiety/depression and graded into three levels (level 1 = no problem; level 2 = some/moderate problem; and level 3 = extreme problem). This study will use a Korean estimate weighted-value model of health-related quality of life [24]

The Health Utility Index III (HUI-III) consists of health measures on sight, hearing, speaking, walking, agility, emotion, cognition, and pain, and quality of life values will be calculated by assigning section results to preference score calculation function following the method suggested by Kopec et al. [25].

Lumbar range of movement (ROM) will also be used to objectively assess improvement after treatment. While ROM evaluation is reliable (*r* = 0.94) and valid (*r* = 0.97) [26], it is not highly responsive (effect size 0.1–0.6) [27]. The angle between a perpendicular line and the patient’s lumbar spine will be measured using a goniometer at maximum lumbar flexion, extension, sidebending, and rotation, respectively. If measurement is not possible due to pain, the angle will be recorded as 0°.

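### Outcome assessment is set after treatment, so momentary measures in weeks 2 to 6 can include that day's session effect; the order at the baseline visit is left unreconciled

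*Protocol article*

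**What the plan says.** The Blinding section gives the only instruction on when an assessment happens relative to a session: "a research nurse or KMD blinded to allocation will conduct outcome assessment in a separate room after treatment". The next sentence, "The patient will also be cautioned against informing the outcome assessor of treatment allocation prior to each assessment", speaks of repeated assessments, which favours a visit-by-visit reading. No section states a pre-session rule or makes an exception for baseline.

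Table 1 (Methods/design) schedules the NRS at weeks 2, 3, 4, 5 and 6, and ODI, PGIC, range of motion, EQ-5D and HUI-III at week 5, all within the treatment period. EQ-5D is described under Secondary outcome measures as having "five dimensions or items assessing current health state". Range of motion is a goniometer reading. Primary outcome measurement defines the NRS as pain over the preceding week, then describes the patient's response as a rating of present pain.

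On the start of the trial, Trial design and study setting gives "6 weeks of outpatient treatment for LBP starting from visit 2 through random allocation". Randomization and allocation concealment says that "Central randomization by phone will be performed through contact upon participant enrollment". Table 1 puts allocation and the baseline measures together at Week 0, leaves the treatment rows empty there, and starts treatment at Week 1 under "Active treatment post allocation".

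**The concern.** The three arms receive different things at a session: manual therapy, physical therapy, or both. If a session briefly changes pain or mobility, an assessment made just afterwards records that change with any lasting effect, possibly by a different amount in each arm. Range of motion is the clearest case, because the lumbar spine is measured after the same region has been treated. The article includes this outcome as an objective check on improvement.

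Baseline matters for a second reason. Patients are not blinded and most outcomes are self-reported. A baseline value taken after the patient knows the arm, or after a first session, would no longer be a pre-treatment value. It enters the within-group paired tests and can enter the secondary ANCOVA. The article does not say that this will happen, but its sections do not together rule it out.

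**Working it through.** **1. Which readings are exposed.** An on-treatment reading is exposed if the visit also has a session and the measure reflects the patient's state at that moment.

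- Range of motion, week 5: momentary by its nature. Exposed.
- EQ-5D, week 5: momentary by the article's description. Exposed.
- NRS, weeks 2 to 6 (five readings): exposed if scored as present pain, much less so if scored over the preceding week. The article says both.
- ODI, PGIC and HUI-III, week 5: nothing in the article ties them to the moment of assessment, so they are not counted.
- Weeks 7, 10 and 14: these fall 7 − 6 = 1, 10 − 6 = 4 and 14 − 6 = 8 weeks after treatment ends. No session is planned, so they are not exposed.

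**2. Weight of week-5 EQ-5D in the QALY.** Economic evaluation uses EQ-5D with an area-under-the-curve method over 14 weeks. Table 1 has EQ-5D at weeks 0, 5, 7, 10 and 14. Assuming straight lines between points, each interior point has weight (next time − previous time)/2, and each end point has half its single interval.

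| Week | Weight (weeks) | Share of 14 |
|---|---|---|
| 0 | (5 − 0)/2 = 2.5 | 17.9% |
| 5 | (7 − 0)/2 = 3.5 | 25.0% |
| 7 | (10 − 5)/2 = 2.5 | 17.9% |
| 10 | (14 − 7)/2 = 3.5 | 25.0% |
| 14 | (14 − 10)/2 = 2.0 | 14.3% |
| Sum | 14.0 | 100% (rounded) |

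The exposed on-treatment reading therefore carries 3.5/14 = 25%. How far the QALY moves also depends on how far the week-5 value is shifted, and the documents do not give this.

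**3. Route to the primary endpoint.** The observed week-7 NRS is unaffected. Statistical analysis fills missing values by last observation carried forward, so a week 2 to 6 reading can stand in at week 7. Sample size plans for 25% dropout: 0.25 × 20 = 5 patients per arm. If all five left with an exposed reading shifted by *s* points, the arm mean would move by (5/20) × *s*. As an assumed range, *s* = 0.25, 0.5 and 1.0 give 0.06, 0.13 and 0.25 points, against the planned difference of 1.5. This is an upper limit at each *s*. It requires every dropout to occur after a week 2 to 6 reading, each last reading to be made after a session, and the NRS to be scored as present pain.

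**4. Order at the start.** Statistical analysis puts the primary endpoint both one week after treatment ends and seven weeks after allocation. Six weeks of treatment plus one week is seven, so the course begins at allocation, with no gap in whole weeks. That agrees with the text that starts treatment at visit 2. Table 1 shows no treatment at Week 0. Neither place gives the order within the day, and the randomisation section ties the telephone call to enrolment without saying whether baseline is complete by then.

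**The case against.** The strongest objection concerns baseline. A reader might infer from the Blinding sentence that baseline values will be taken after the first session. The documents do not support that. Table 1 places the baseline measures at Week 0, where the treatment rows are empty, and the analysis calls its within-group comparison pre-post. There is also a screening NRS at Week −1. What remains is that the text on visit 2 points the other way and the two are not reconciled. The screening value covers only the NRS. The other baseline measures have no earlier reading.

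A reader might also add the baseline weight to the week-5 weight, giving 17.9% + 25.0% = 42.9%, and conclude that about 43% of the economic result is compromised. That sum depends on the unsupported baseline reading and treats a weight as a bias. The economic analysis is also exploratory.

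The phrase about treatment could be read as describing only how assessors are kept apart from it. That is possible, but the following sentence about each assessment favours the per-visit reading, and sites have no other timing instruction. An article may leave visit procedures to a fuller protocol. However, this article does state an order, so the point concerns what it says and not what it omits.

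It is tempting to argue that assessing after a session gives the assessor more cues to the arm. Nothing in the documents establishes this. The separate room, the assessor's absence from treatment and the caution to patients all work against it.

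**Conclusion.** The concern holds in a limited form. Assessment after the day's session exposes week-5 range of motion and EQ-5D to a same-day effect that may differ by arm. It exposes the week 2 to 6 NRS as well if that is scored as present pain. Week-5 EQ-5D has a 25% weight in the 14-week QALY, assuming linear interpolation. The conclusion rests on the visit-by-visit reading and on assessment visits that also contain a session. The size of any bias is unknown, so the article permits such an effect but does not show one.

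The primary comparison is largely protected. It can be reached only through carried-forward values, and the preceding-week definition of the NRS dampens even that route. Baseline is an unreconciled ambiguity about order. This is a cheap improvement to a pilot trial and not a threat to its primary result.

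**What to change.** 1. In Blinding, replace the timing phrase so that, at any visit with both an assessment and a session, the outcome assessment is completed before that day's session in all three arms, still in a separate room and by the blinded assessor.
2. Reconcile Table 1, Trial design and study setting, Randomization and allocation concealment, and Blinding, so that all baseline assessments are completed before the allocation call and the first session.
3. In Primary outcome measurement, state one recall period for the NRS. This settles how far the weekly readings are exposed.

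The cost is a few sentences and a small scheduling change, because the assessor must be available before the session. Visits, staff and treatment stay the same. For visits already held, the order cannot be changed, but the report can state which order was used.

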### Interventions

#### Chuna manual therapy (see Additional file ***3*** for technical details with photos)

A semistandardized *Chuna* treatment plan for LBP was established by technique selection based on specialist opinion collected through survey of *Chuna* clinical specialists (total *n* = 20) [14] and physicians employed at a spine-specialty designated Korean medicine hospital [15]. The physicians administering *Chuna* in this trial will be KMDs with 3+ years’ clinical experience of *Chuna* manual therapy use, and will be deployed after receiving *Chuna* protocol training sessions (two sessions, 4+ h/session) for standardized application. *Chuna* covers a wide variety of techniques including high-velocity, low-amplitude thrusts to joints, slightly further than the passive range of motion, and mobilization which applies manual force to joints in the passive range of motion [16]. The *Chuna* techniques utilized in this study are divided into lumbar and pelvic regions, and mandatory or selective techniques will be performed following physician judgement (Table 2).

**Table 2 Tab2:** Semistandardized treatment plan of study *Chuna* techniques [38–41]

Region	Mandatory techniques	Selective techniques
Lumbar spine^a^	• Spine flexion distraction technique (flexion) • Sidelying lumbar (extension or flexion) dysfunction correction technique	• Spinal flexion distraction (circumduction) • Spinal flexion distraction (sidebending) • Iliopsoas fascial *Chuna*
Pelvis^a^	<Iliac dysfunction (if applicable by evaluation) > • Prone iliac anterior rotation dysfunction correction technique/ or • Prone iliac posterior rotation/sacral sidebending dysfunction correction technique • Prone leg raise iliac dysfunction correction technique • Prone inflare-outflare dysfunction correction technique < Sacral dysfunction (if applicable by evaluation) > • Prone sacral sidebending and rotation dysfunction correction technique	• Prone sacral dysfunction correction technique (extension or flexion)

^a^Dysfunction type assessed and diagnosed prior to treatment

A total of 10–18 *Chuna* manual therapy sessions (at least 10 sessions or more are required to be received by participants) will be administered over a 6-week period. Frequency of treatment will differ by period with two to three sessions/week from week 1 to week 4, and one to three sessions/week from week 5 to week 6 based on *Chuna* physician judgement of previous treatment results. The time duration of one *Chuna* manual therapy session will be approximately 15 min including evaluation and treatment.

#### Usual care

Conventional usual care will be limited to orally administered medicine, physical therapy, and back pain care education (15-min education with visual aids covering cause, prevention, management, and exercise for back pain care) in this study. Medication and physical therapy of usual care will be provided with reference to most common treatments used in LBP-related patients as assessed from 2011 Korean Health Insurance Review and Assessment (HIRA) statistics [17] or clinical practice guidelines, provided as lists of most frequent medicine and physical treatments to the usual care physician [5]. Participants will be asked to record drug intake to monitor adherence, and medicine and physical therapy usage type and frequency will be recorded in a separate Case Report Form (CRF) for outcome assessor blinding purposes.

#### Combined Chuna manual therapy and usual care

The combined treatment group of *Chuna* manual therapy and usual care will receive both treatments in the same method, frequency, session length, total duration, and number of sessions of each treatment as that of the other two groups.

#### Cointerventions

Additional treatment (e.g., other medication related to pain, acupuncture, procedures or surgery) other than that specified in the protocol will not be allowed during the 6-week intervention period.

### Outcomes

#### Primary outcome measurement

The primary outcome will be LBP level for the past week assessed using the NRS. In the NRS, the participant selects a number from 0 to 10 that best indicates current pain level (with 0 indicating no pain, and 10 the most severe pain one can imagine) [18, 19].

#### Secondary outcome measures

Secondary outcome measures include leg pain level for the past week as assessed using the NRS. Functional status will be evaluated using the Oswestry Disability Index (ODI) questionnaire. The ODI is a 10-item questionnaire developed for the purpose of LBP-related disability assessment [20]. Each item has a six-level answer choice, and each level correlates with a score of 0–5. Higher scores reflect greater disability. The accredited Korean version of the ODI [21] will be used. The Patient Global Impression of Change (PGIC) will be assessed for comprehensive and global assessment of change in LBP and movement limitation due to pain [18, 22]. The PGIC discerns subjective impression of change in seven levels ranging from 1 = very much improved; 2 = much improved; 3 = minimally improved; 4 = no change; 5 = minimally worse; 6 = much worse; to 7 = very much worse. While the PGIC was initially developed for psychological use, it is currently applied in pain evaluation of various medical fields. The EuroQol-5 dimensions (EQ-5D) health survey is a measurement tool for health-related quality of life and widely used across the health care sector. The range of scores is from −1, indicating health considered worse than death to 1, meaning perfect health [23]. The EQ-5D comprises five dimensions or items assessing current health state, which are mobility, self-care, usual activities, pain/discomfort, and anxiety/depression and graded into three levels (level 1 = no problem; level 2 = some/moderate problem; and level 3 = extreme problem). This study will use a Korean estimate weighted-value model of health-related quality of life [24]

The Health Utility Index III (HUI-III) consists of health measures on sight, hearing, speaking, walking, agility, emotion, cognition, and pain, and quality of life values will be calculated by assigning section results to preference score calculation function following the method suggested by Kopec et al. [25].

Lumbar range of movement (ROM) will also be used to objectively assess improvement after treatment. While ROM evaluation is reliable (*r* = 0.94) and valid (*r* = 0.97) [26], it is not highly responsive (effect size 0.1–0.6) [27]. The angle between a perpendicular line and the patient’s lumbar spine will be measured using a goniometer at maximum lumbar flexion, extension, sidebending, and rotation, respectively. If measurement is not possible due to pain, the angle will be recorded as 0°.

#### Cost data investigation

Costs associated with health care may be largely divided into three categories: medical, nonmedical, and lost productivity cost [28–30]. Medical cost covers direct expenses incurred by the use of medical facilities and services (official medical cost) and purchase of health foods and medical devices (unofficial medical cost). Nonmedical cost refers to accompanying costs incidental to medical use such as transportation, patient time, and nursing costs. Lost productivity cost represents economic loss from decreased work capability because of the disease itself or premature death due to disease. Cost data for economic evaluation will be collected through structured survey of medical, nonmedical, and lost productivity cost categories (basic items will be included or excluded according to period).

